## 3. Discussion

The aim of this double-blind randomized sham surgery controlled clinical trial is to investigate the efficacy of an intra-articular injection of tSVF, as an adjuvant to arthrocentesis, in reducing pain and increasing mouth opening in TMJ osteoarthritis patients.

A tSVF injection in the TMJ is categorized as cellular therapy, which has consequences on its medical ethical approval and its regulatory burden. tSVF obtained through mechanical fractionation can be considered as being minimally manipulated, contrary to enzymatically digested cellular stromal vascular fractions (cSVFs). The European Medicines Agency considers a product not substantially manipulated when it ‘does not contain cells that have been subject to substantial manipulation so that biological characteristics, physiological functions, or structural properties relevant for the intended clinical use or for the intended regeneration, repair or replacement have been altered’ [46]. However, since we will inject adipose-derived SVFs into the donor patient’s TMJ space, it will not contain ‘cells that are intended to be used for the same essential function(s) in the recipient and the donor’ [46]. This heterologous application categorizes tSVF as a cellular therapy, i.e., an advanced therapy medicinal product (ATMP). Although the safety of intra-articular SVF injections has been proven and well-documented [47,48,49], national medical ethical committee approval can only be obtained by strictly adhering to the rules for cellular therapy products. Quality control is essential since tSVF composition is variable between donors, and this can influence the treatment’s effect. However, tSVF is a heterogenous product with an intact extracellular matrix, which makes it difficult to characterize with conventional single-cell suspension characterization assays since the cells are bound to the extracellular matrix. The tSVF will be injected during the same surgical procedure immediately after fractionation, which makes it impossible to undertake a quality control before the injection. Medical ethical approval demands testing of whether tSVF components are present in pre-defined concentrations. This criterion implies, however, that certain separate components of tSVF are responsible for its clinical efficacy. Yet it is also possible that the synergy of the components of tSVF is responsible for its clinical efficacy. Nevertheless, at this point in time, we do not know whether specific tSVF components are responsible for its mechanism of action, i.e., the suppression of inflammation, or which components those might be. Hence, it is impossible to determine the acceptable concentration range of the tSVF components to pass the quality control. In addition to this, since the tSVF will be injected intra-operatively immediately after fractionation, controlling its quality will only be possible after being injected into the TMJ, while most cellular ATMPs need to be quality-assessed before administration.

The SVF is obtained through adipose tissue processing. Adipose tissue harvested through a liposuction procedure consists of two fractions: adipocytes and SVF. tSVF is produced through mechanical fractionation by forcing the adipose tissue through a device with a small hole and centrifuging it twice to disrupt the adipocytes and remove the oil [22]. Our recent scoping review showed that the first centrifugation step is especially essential to remove oil from the adipose tissue by adequately disrupting the adipocytes to release their triglycerides [22]. In a trial, we used the FAT procedure to yield tSVF consisting of a heterogeneous mixture of endothelial cells, pericytes, preadipocytes, fibroblasts, macrophages, and adipose-derived stromal cells (ASC), while preserving the intercellular connections, including the extracellular matrix [50]. The extracellular matrix functions as a slow-release platform for factors secreted by these cells and probably results in longer cell survival [51].

The hypothesized mechanism of action of tSVF in a chronically low-grade-inflamed osteoarthritic joint is that the cells secrete anti-inflammatory factors in a paracrine fashion, which downregulates inflammation. Since the cells will probably not be engrafted in the joint, cartilage regeneration is not expected to occur. Testing this hypothesis is necessary to understand its mechanism of action better. We will therefore test the synovial fluid at both baseline and after 26 weeks for pro-inflammatory and anti-inflammatory factors in both the intervention and the control group. We expect that tSVF will reduce potentially harmful factors such as IL-1B, TNF-alpha, chemoattractants, and MMPs, as well as PGE2, one of the most important factors that maintains the chronic inflammation in the joint. In addition to this, we pose that tSVF, through the secretion of growth factors such as FGF, VEGF, IGF, and HGF, sets the local micro-environment into ‘regenerative mode’ by putting activated synoviocytes into rest mode. There is no synovial fluid analysis data available from TMJ osteoarthritis patients after a tSVF injection. However, in a study of patients with knee osteoarthritis, a reduction in pro-inflammatory molecules (MMP-2, IL-1B, IL-6, and IL-8) and an increase in anti-inflammatory molecules (IGF-1 and IL-10) were found at the 1-year follow-up after an SVF injection [21]. However, performing an additional arthrocentesis for synovial fluid analysis in the recovering joint after 26 weeks to test the mechanism of action for scientific reasons could be considered unethical since there is no benefit for the patient. Nonetheless, because these adipose-derived regenerative treatments are still in their early stages, testing their mechanisms of action is often required to obtain medical ethical approval.

There are some limitations to this trial: we will not investigate which tSVF dosage should be injected, the number of injections that would be sufficient, whether differences in patient characteristics influence the efficacy of autologous tSVF, nor whether the stage of the disease influences the treatment potential. We chose to use sham surgery in the form of making a small stab incision in the control group in this study design. However, since no bruising will occur because no liposuction will be performed, the patients will be able to deduce their treatment allocation. We decided not to perform a complete liposuction procedure in the control group because this would impose unnecessary treatment-related side effects.

The first two human trials of injecting adipose-derived components showed a reduction in pain and increased mouth opening [26,27]. However, the methodological quality of these non-controlled trials was low. A recent randomized controlled trial compared a control arthrocentesis group with an experimental group injected with micro-fragmented adipose tissue obtained by the Lipogems procedure [28]. This method leads to adipose cluster reduction by using metal balls in a device which does not disrupt all the adipocytes and is therefore not similar to our FAT procedure, which produces tSVF [52]. Both pain (VAS) and mouth function (interincisal opening) were measured preoperatively and during the follow-ups 10 days, 1 month, and 6 months after the injection. The trial reported that the experimental group had a notable reduction in pain at both the 10-day and 1-month follow-ups but the mouth opening only began to improve 6 months after the injection. This result suggests that adipose tissue injection leads to immediate pain reduction, but mouth opening only improves after 6 months. Pain reduction and functional improvement have also been seen with osteoarthritic knees following this procedure [15,53,54,55]. To our knowledge, there are no animal trials describing the injection of tSVF in TMJ osteoarthritis models. However, animal trials have shown increased cartilage thickness after adipose-derived stromal cell injections compared to control groups, a finding that has not been confirmed in human trials [56]. The safety of intra-articular injections in knee osteoarthritis has been well proven. A recent systematic review noted few minor complications and one major complication after 4008 knee injections; there was one case of knee joint infection which was treated successfully by means of a synovectomy and antibiotics [49]. Following 264 intra-articular injections, only 7 minor complications and no serious adverse events were reported [47]. After 480 knee injections, one patient had symptoms of transient pain and swelling, but the symptoms resolved spontaneously and subsequent injections were uneventful [57].

In conclusion, our double-blind randomized sham surgery controlled clinical trial will investigate whether a tSVF injection, as an adjuvant to arthrocentesis, will reduce the symptoms in TMJ osteoarthritis patients and increase their mouth opening. This may potentially lead to new treatment options for TMJ osteoarthritis.

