### 2.3. Trial Design

This study is planned as a prospective double-blind randomized sham surgery controlled clinical trial. It will be an intervention study with a parallel design consisting of even treatment allocations (ratio of 1:1). All consecutive patients visiting the Department of Oral and Maxillofacial Surgery at the University Medical Center Groningen, The Netherlands, with osteoarthritis of the TMJ will be assessed for eligibility based on the inclusion and exclusion criteria mentioned in Table 1. It is estimated that acquiring the required number of patients suitable for inclusion will take around 1–2 years. The follow-up period will be 1-year post-intervention.

Patients will be included in the study after being evaluated by an oral and maxillofacial (OMF) surgeon who will then schedule them for baseline assessments by the investigator of pain, maximal interincisal opening (MIO), and collection of all the questionnaires (VAS, MFIQ, OHIP-49, SCL-90). The investigator will be blinded regarding treatment allocation during the entire study. After the baseline assessment, randomization will take place (minimization randomization; ALEA, Abcoude, The Netherlands). Both groups will be scheduled for an intervention at the Oral Maxillofacial Surgery outpatient clinic of the University Medical Center Groningen, The Netherlands. An envelope with the treatment allocation will only be handed to the OMF surgeon on the day of surgery.

The patients will not be informed about the treatment allocation. However, since the intervention group will receive an additional liposuction procedure, they could derive their treatment allocation from this additional procedure. Hence, a sham liposuction procedure will be performed on the other group’s patients by preparing a sterile surgical field on the abdomen, making a small stab incision, and then putting a medical plaster on the incision site. The control group patients will be informed about possible liposuction-related symptoms in the same manner as the intervention group patients receiving the actual liposuction. We will not perform the complete liposuction procedure in the control group for ethical reasons. Since the OMF surgeons perform the surgery, they will be informed about the treatment allocation.

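### The trial is called double-blind, yet the article says patients will be able to work out their arm, and the primary outcome is the patient's own pain rating

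*Protocol article*

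**What the plan says.** Section 2.3 of the protocol article sets the label: "This study is planned as a prospective double-blind randomized sham surgery controlled clinical trial". The opening paragraph of Section 3 repeats it, and so does the conclusion: "our double-blind randomized sham surgery controlled clinical trial will investigate whether a tSVF injection".

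Three groups of people could be masked, and the article deals with each:

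- **Patients.** Section 2.3 says "The patients will not be informed about the treatment allocation". It recognises that liposuction could reveal the arm, and so gives controls a sterile abdominal field followed by "making a small stab incision, and then putting a medical plaster on the incision site". It also says "The control group patients will be informed about possible liposuction-related symptoms in the same manner" as patients who have the real procedure. The limitations paragraph of Section 3 then says that "since no bruising will occur because no liposuction will be performed, the patients will be able to deduce their treatment allocation".
- **Surgeons.** "Since the OMF surgeons perform the surgery, they will be informed about the treatment allocation" (Section 2.3). They also examine patients for complications at follow-up.
- **Investigator.** "The investigator will be blinded regarding treatment allocation during the entire study" (Section 2.3).

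Section 2.1 names the VAS as the primary endpoint. Section 2.3 lists it with the MFIQ, OHIP-49 and SCL-90 among the questionnaires collected. Mouth opening is measured with a calliper (Section 2.6).

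**The concern.** The sham exists to stop patients inferring their arm from the abdominal procedure. The limitations paragraph says, without hedging, that patients will be able to infer it anyway, and the conclusion a few paragraphs later still calls the trial double-blind. Both statements are current text and they do not agree.

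This matters because of the type of primary outcome. When patients rate their own pain, they are the assessors. A masked investigator who hands over the form protects the calliper measurement well, but gives little protection to the VAS, MFIQ or OHIP. If controls conclude that they had no liposuction, and therefore no tSVF, disappointment could raise their scores. Treated patients who see bruising could report less pain because they expect benefit. A difference in VAS would then mix the effect of tSVF with the effect of knowing the arm, while the label tells readers that patient blinding has removed the second.

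**Working it through.** **Step 1. Compare the label with the text.**

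| Party | Masking described | Role in the primary outcome |
|---|---|---|
| Patient | Attempted by sham; stated to be deducible (Section 3) | Rates VAS pain |
| Surgeon | None (Section 2.3) | Operates; examines for complications |
| Investigator | Throughout (Section 2.3) | Collects the questionnaires, measures mouth opening |

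Only one of the three is reliably masked, and that one does not generate the primary outcome.

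**Step 2. Reproduce the planned sample size, to establish the precision of the VAS comparison.** Inputs from Section 2.8: Z values 1.96 and 0.84, σ = 0.94, T = 4, ρ = 0.7, v = 0.8, ratio 1:1.

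n = (1.96 + 0.84)² × 2σ² × [1 + (T − 1)ρ] / (T v²)

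- [1 + 3 × 0.7] / 4 = 3.1 / 4 = 0.775
- n = 7.84 × 2 × 0.8836 × 0.775 / 0.64 = 16.78

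This agrees with the stated 16.8, rounded to 17 per group. The calculation itself is not in question.

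**Step 3. Standard error of the averaged difference.** SE = √(2 × 0.775 × 0.94² / n).

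- 17 per group: SE = 0.284
- 20 per group (the planned recruitment): SE = 0.262

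**Step 4. What a reporting bias would do.** Suppose tSVF has no true effect and knowledge of the arm shifts mean VAS between groups by b, equally at all four visits. Then

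P(significant) = Φ(b/SE − 1.96) + Φ(−b/SE − 1.96)

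| Assumed b | Share of the planned 0.8 | 17 per group | 20 per group |
|---|---|---|---|
| 0 | 0% | 5% | 5% |
| 0.1 | 12.5% | 6.4% | 6.7% |
| 0.2 | 25% | 10.9% | 11.9% |
| 0.3 | 37.5% | 18.5% | 20.9% |
| 0.4 | 50% | 29.1% | 33.3% |

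The values of b are assumptions; the documents give no figure. Constancy over time is a second assumption, and it matters. A shift of 0.4 at week 3 that was gone by weeks 12, 26 and 52 would average 0.4 / 4 = 0.1, which is the 6.4% to 6.7% row.

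**The case against.** The strongest reply is that the authors hide nothing. Section 3 states the weakness as a limitation and explains it: full liposuction would impose unnecessary side effects on controls. Section 2.3 gives the ethical reason and says openly that surgeons know the arm. This stands, and it is why the point concerns the label and the claim, not the choice of sham. It does not remove the conflict, because the design section and the conclusion still assert the property that the limitations paragraph denies.

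Three stronger readings are tempting, and the article does not support them:

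- **That patients are simply unmasked.** They are not told their arm, controls have a prepared field, an incision and a plaster, and both arms receive 1 mL through the same needle after arthrocentesis (Section 2.5). Blinding is attempted and partial. That giving both arms the same information about symptoms makes the absence of bruising more telling is plausible, but it is an inference.
- **That the plan has no check on blinding.** The article mentions none, but it condenses a fuller protocol that is not shown. Its silence cannot be counted as a gap.
- **That the false-positive rate is about 30%.** That figure needs a shift of 0.4 sustained for a year, and nothing in the documents establishes either part.

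A reader might also want to use the calliper measurement as the arbiter, discounting any VAS effect that mouth opening does not support. Section 3 argues against this. It reports a related trial in which pain fell at 10 days and 1 month while mouth opening improved only at 6 months. Early discordance could therefore occur with a real effect. The sample size was also set for pain, so mouth opening could miss a true benefit.

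**Conclusion.** The concern holds as an inconsistency in the stated level of blinding, with a consequence for what the primary result can show. By the article's own statements, reliable masking extends only to the measuring investigator, while the primary endpoint and two of the secondary ones (MFIQ, OHIP) are reported by patients who are expected to be able to deduce their arm. A VAS difference may therefore partly reflect expectation.

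The size is not known. Under the assumptions in the working (no true effect, constant shift of 0.1 to 0.4, the article's variance inputs), the false-positive rate would be about 6–29% at 17 per group or 7–33% at 20 per group, against a nominal 5%. These figures show how sensitive the comparison is; they do not estimate the bias in this trial.

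Because the limitation is disclosed with its reason, and no sample size or analysis is wrong on this account, the point should be fixed but is not a bar to proceeding.

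**What to change.** 1. In Section 2.3 and in the opening and concluding paragraphs of Section 3, replace the double-blind label with *investigator-blinded, sham-controlled, with attempted (partial) patient blinding*. *Outcome-assessor-blinded* would be wrong here, since the patient assesses the primary outcome.
2. State alongside it that the primary VAS result is not protected by reliable patient blinding and will be interpreted accordingly.
3. If the full protocol does not already have one, add a single treatment-guess question with the reason for the guess, asked after the VAS at the existing week-3 visit. Report it descriptively by arm with a blinding index. Week 3 is preferable to week 52, when a guess is more likely to reflect perceived benefit. For the same reason, and because about 20 patients per arm would be split further, do not rely on VAS effects within guess groups.
4. Do not make agreement with mouth opening a decision rule. At most, discuss it as interpretation at weeks 26 and 52.

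The cost is wording, one extra question at an existing visit, a less favourable design label and a more cautious claim. Section 2.2 says approval is pending, so the change can still be made before the trial starts. It alters neither treatment nor the sham.

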## Figures and Tables

**Figure 1 bioengineering-11-00171-f001:**
[figure not shown]
The pathogenesis and hypothesized mechanism of action of tSVF injection on TMJ osteoarthritis. (arrow up means higher concentration; arrow down means lower concentration).

**Figure 2 bioengineering-11-00171-f002:**
[figure not shown]
Follow-up.

**Figure 3 bioengineering-11-00171-f003:**
[figure not shown]
Inclusion test.

**Table 1 bioengineering-11-00171-t001:** Inclusion and exclusion criteria.

Inclusion	Exclusion
Age between 18 and 70 years Chronic nociceptive pain in the TMJ region, aggravated by protrusion, maximal mouth opening, lateral excursions, and/or chewing for at least 2 months Wilkes stages III or IV (internal derangement) Limited maximal interincisal opening (<35 mm and >15 mm) Pain still present after two weeks of an NSAID (i.e., ibuprofen 600 mg three times daily or diclophenac 50 mg 3 td or naproxen 500 mg 2 td) Pain disappears after diagnostic intra-articular injection of local anesthetic	Edentulous (no dentition) Concurrent use of anti-inflammatory medication, steroids, muscle relaxants, or antidepressants Previous TMJ traumas and fractures Previous TMJ surgeries, previous intra-articular injections within <1 year Previous osteotomies of the mandible Bilateral severe TMJ derangements Bony or fibrotic ankylosis of the TMJ Known history of diabetes mellitus type 1 or 2 Known history of HIV Known history of Hepatitis B or C Serious systemic diseases, rheumatic disease, or infectious/inflammatory diseases affecting the skin of the TMJ area Pregnancy Coagulation disorders BMI < 15
